## Discussion

The study will have a significant impact by establishing a referral pathway that integrates disparate parts of the private healthcare system, facilitating the early diagnosis of chronic conditions such as diabetic retinopathy (DR). The long-term goal is to create a cost-effective pathway for the management of DR. We plan to publish these findings in top peer-reviewed journals and present them at reputable conferences. Finally, the participating healthcare institutions (LVPEI and IDEA clinics) are committed to institutionalizing the pathway into their routine operations to provide higher-quality care to their patients.

### Strengths of the study

• Establishment of a systematic DR screening program at physician clinics, improving early detection and management of diabetic retinopathy.• Utilization of various fundus cameras to evaluate the scalability, adaptability, and accuracy of the DR screening system.• Development of an effective imaging pathway to enhance accuracy and reduce ungradable images.• Completion of the referral pathway and creation of a universally implementable tracking system.• Analysis of the economic impact, cost-effectiveness, and environmental impact of tele-DR screening.

### Limitations of the study

• The study is conducted in a private healthcare setup where costs are involved, which may result in the exclusion of some patients who could not afford the screening, potentially leading to missed enrolments.• The use of non-mydriatic fundus photography may limit the quality of imaging due to undilated pupils, potentially affecting the accuracy of DR detection.• The study is not designed as a randomized controlled trial (RCT), which would have required the involvement of multiple health facilities and diabetes clinics to generalize the findings more broadly.

The implementation of the study may face challenges such as variability in AI performance, patient adherence to referrals and follow-up, operational issues across multiple sites, patient acceptance of AI tools, and resource constraints for scale-up. To address these potential challenges, we plan periodic recalibration of the AI system, standardized technician training, and regular quality audits to ensure consistent performance. Technicians will undergo periodic training programs focused on image acquisition techniques, device handling, and identification of common image quality issues. In parallel, we will maintain regular communication with the AI solution providers to incorporate necessary adjustments in the algorithm, particularly to optimize performance based on real-world sensitivity and specificity data. This dual approach is expected to enhance both image quality and the diagnostic accuracy of the AI system over time. Strategies to improve patient adherence will include employing navigators, simplifying referral pathways, and providing education on the importance of timely care. Operational issues will be managed through centralized coordination, cloud-based data management, and regular equipment maintenance. Patient trust in AI tools will be fostered through education, validation of AI outputs by experts, and sharing of success stories. Resource constraints will be mitigated by phased implementation in high-burden areas and leveraging public-private partnerships.

Additionally, ensuring adherence to the **Standard Operating Procedure (SOP)** in a private clinic chain—where business performance may take precedence—can be challenging, as operational priorities may not always align with clinical protocols. Furthermore, monitoring compliance across multiple locations is complex due to variations in workflow, staff engagement, and resource availability. Adherence to SOPs in a private clinic chain with business priorities will be ensured by aligning protocols with clinic goals, incentivizing compliance, and integrating them into existing workflows. Stakeholder engagement and automated compliance tracking will further support adherence. Monitoring across multiple locations will be managed through real-time dashboards, automated alerts, remote audits, and periodic site visits. Local champions will be designated in each clinic to enhance accountability and streamline implementation. These measures are expected to support effective and scalable implementation of the study.

Given that private providers manage 70–80% of all patients, with an even higher proportion in advanced ophthalmologic conditions like DR, the findings are highly relevant to real-world care delivery. The study’s reliance on private healthcare clinics may limit generalizability by excluding patients unable to afford screening. To reduce selection bias, future studies should include public healthcare settings. Non-mydriatic fundus photography may impact image quality and DR detection accuracy; this can be mitigated through enhanced technician training, image quality audits, and advanced AI algorithms. These steps can improve the applicability of findings across diverse settings.

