**Fig 3 pone.0324382.g003:**
[figure not shown]
Study flow chart.

We will invite eligible patients for screening through a call and recall system. Visual acuity in both eyes will be recorded using a tablet with a web-based vision checking application (Peek Vision). Non-mydriatic fundus photography of both eyes will be performed using AI-integrated retinal cameras (Forus, 3 Nethra Classic HD with AI Integration in two facilities, and Remidio, Fundus on Phone with AI integration, in two facilities). These AI tools have undergone internal validation and published by the company prior to its integration into the cameras [30,31]. Our project, we will be conducting a real-world validation to assess the performance and effectiveness of this AI tool in practical clinical settings.

Diabetic retinopathy grading will be conducted as per International Clinical Diabetic Retinopathy severity scale [32]. Sight-threatening diabetic retinopathy (DR) is defined as severe non-proliferative diabetic retinopathy (NPDR), proliferative diabetic retinopathy (PDR), and moderate to severe diabetic macular edema (DME). The referral criteria include any patient with DR, visual acuity less than 20/60, any other retinal pathology requiring referral, or ungradable retinal images, or any combination of these factors.

In the AI-enabled screening process for Diabetic Retinopathy (DR) using fundus images, if no signs of DR are detected by the AI, the patient will receive a label of “no DR diagnosis” at the initial stage. However, if DR is indicated, a trained technician at the Idea Clinic will manually review the images to confirm or rule out DR, and the result will be communicated to the patient by the physician. Simultaneously, all images will undergo further manual grading at the Central Image Reading Center at LVPEI for quality assurance. If this manual grading results in a change in diagnosis, the updated result will be shared with the patient within a week since their initial screening.

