### Quality assurance, quality control measures

To ensure rigorous quality assurance and control, the study will include comprehensive technician training with quarterly refreshers and bi-monthly calibration of AI screening equipment. Comprehensive training programs will be provided to non-medical technicians, focusing on the correct use of AI-assisted screening equipment, standardized procedures for visual acuity tests, and accurate capture of fundus photographs. Technicians at diabetes clinics will be trained in visual acuity estimation and validation tests (n = 25) to ensure reliability and accuracy. The visual acuity tool used in the study (Peek Vision) has been globally validated in multiple studies and effectively utilized by technicians and field workers in diverse settings [33,34]. The sample size of **N = 25 patients (50 eyes)** is intended for pilot testing following standardized training. This pilot will serve as an initial assessment of the reliability and accuracy of visual acuity estimation using the mobile VA application by trained technicians. The pilot testing results will be used to validate the training protocol and identify any gaps requiring refinement.

To ensure ongoing reliability, periodic audits will be conducted during training refresher programs, where technicians’ performance will be re-evaluated. Additionally, comparisons of visual acuity estimates from referred patients will be performed to assess consistency over time. This iterative approach ensures that the quality of visual acuity measurements is maintained throughout the study. They will also receive training in fundus image capture, study image protocol, DR grading and referral criteria.

Quality control measures will be implemented to monitor and verify the accuracy of DR and STDR detection rates, timely referral rates, and other key metrics. A quality assurance process will compare AI grading with manual grading by the technician and the Central Reading Center to ensure screening accuracy and reliability.

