### Statistical analysis

Accuracy of AI-enabled cameras: Taking the grading of images done by the experts as the ground truth, we will estimate the accuracy of the AI- enabled cameras (operated by a non- ophthalmic technician) using standard measures such as sensitivity, specificity, and area under the ROC (Receiver Operating Characteristic). Multivariable regression models will be employed to adjust for potential confounders, including age, diabetes duration, baseline visual acuity, and other relevant factors. These models will allow for a more accurate assessment of the relationships between the intervention and key outcomes, such as disease staging at diagnosis, referral rates, and long-term visual outcomes, by accounting for the influence of these confounders. Both linear and logistic regression models will be used, depending on the nature of the outcome variable, to ensure robust and reliable results. Additional statistical tests, such as chi-square tests for categorical outcomes and t-tests or ANOVA for continuous outcomes, will be employed as appropriate.

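### The plan allows the AI algorithm to be adjusted on accuracy data while the same study validates it, so the single accuracy estimate may mix versions and describe none of them

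*Protocol article*

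**What the plan says.** Study procedures describes AI tools already built into two vendors' cameras ("Forus, 3 Nethra Classic HD with AI Integration in two facilities"; the other vendor's "Fundus on Phone with AI integration, in two facilities"). It states that "we will be conducting a real-world validation to assess the performance and effectiveness of this AI tool in practical clinical settings".

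Statistical analysis gives the accuracy method: "Taking the grading of images done by the experts as the ground truth, we will estimate the accuracy of the AI- enabled cameras", with sensitivity, specificity and area under the ROC curve as measures. Program outcomes and its Table 1 list these as outcomes. Sample size plans one estimate of each at 80%, with a 95% confidence level and ±5 points. That requires 246 DR-positive and 246 DR-negative cases, and 1230 patients screened at 20% prevalence.

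Limitations of the study lists challenges to implementing the study, variable AI performance among them. In response it says "we plan periodic recalibration of the AI system". It adds that regular contact with the AI providers will serve to "incorporate necessary adjustments in the algorithm, particularly to optimize performance based on real-world sensitivity and specificity data". Together with technician training, this is expected to "enhance both image quality and the diagnostic accuracy of the AI system over time".

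**The concern.** A validation estimates the accuracy of a defined test. Here the test may be changed in response to accuracy results while its accuracy is being measured, and the plan expects that accuracy to rise. The quantity that the sample size treats as one fixed proportion is then expected to move.

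Two consequences have to be kept apart.

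- **Mixing.** Pooling over versions gives a weighted average that may match neither the earlier algorithm nor the one in use at the end.
- **Optimism.** If images that guided an adjustment also enter the adjusted version's accuracy, that version is judged partly on its own tuning data.

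The Conclusion offers the accuracy evidence to inform policy on reimbursing AI-assisted screening. A figure that belongs to no identifiable version supports that use poorly. Recruitment has run since March 2024 (Study timeline), and versions not recorded when images are scored become harder to reconstruct.

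**Working it through.** **1. The plan's own figure.** Inputs from Sample size: p = 0.80, half-width d = 0.05, 95% confidence (z = 1.96), prevalence 0.20.

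n = z² × p(1−p) / d² = 3.8415 × 0.16 / 0.0025 = 245.85, rounded up to 246. Total = 246 / 0.20 = 1230.

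Both figures reproduce exactly. They hold for one fixed tool.

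**2. Precision per version for sensitivity.** The article gives no number of updates, so k equal-sized versions is an assumption. Half-width = 1.96 × √(0.16 / (246/k)).

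| k | DR-positives per version | Half-width (points) |
|---|---|---|
| 1 | 246 | ±5.0 |
| 2 | 123 | ±7.1 |
| 3 | 82 | ±8.7 |

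Keeping ±5 points for sensitivity in each version would need 1230 × k screened, which is 2460 for two versions.

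**3. Specificity is less exposed.** Screening 1230 at 20% prevalence yields 1230 − 246 = 984 DR-negatives. Two equal versions have 492 each: 1.96 × √(0.16/492) = ±3.5 points. The loss of planned precision is therefore mainly in sensitivity.

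**4. Mixing.** Suppose, for illustration only, that sensitivity moves from 80% to 90% after one update.

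- Half the cases before the update: 0.5 × 80 + 0.5 × 90 = 85%.
- A quarter before: 0.25 × 80 + 0.75 × 90 = 87.5%.
- Three quarters before: 0.75 × 80 + 0.25 × 90 = 82.5%.

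The pooled value depends on when the update happened. It lies above the pre-update version and below the updated one.

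**5. Size of optimism, if it arises.** This was simulated with 1,000 replicates of a binormal model with true sensitivity and specificity of 80%. The cut-off was chosen to maximise their sum and then scored on the same images. Optimism is the apparent minus the true average of sensitivity and specificity.

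| Positives / negatives used for tuning | Apparent | True | Optimism (points) |
|---|---|---|---|
| 246 / 984 | 80.7% | 79.8% | 0.9 |
| 123 / 492 | 81.0% | 79.6% | 1.4 |
| 60 / 240 | 81.7% | 79.4% | 2.3 |

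The model tunes a single cut-off only. If each image keeps the output of the version live at screening, and an updated version is judged only on later patients, this optimism does not arise.

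**The case against.** The strongest reply is that the documented workflow protects the estimate. Under Study procedures the AI labels the image at screening and the central reading centre grades it in parallel. The natural test result is thus the output of the version then in use. Nothing says that earlier images would be re-scored by an adjusted algorithm. This stands. A reader might infer that the estimate is optimistic, but the article does not establish it. With live outputs and rising accuracy, the pooled value would understate the final version.

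Second, the limitations text gives no date or number of updates, does not say outright that the real-world data are this study's, and sits beside measures for later scale-up. This stands in part. The sentence answers challenges to implementing the study, and the only source of real-world accuracy data that the article describes is the study's own comparison of AI with manual grading. Study data during the study is the natural reading, though not a literal statement. The "bi-monthly calibration of AI screening equipment" in the quality assurance section may concern hardware only, and nothing here rests on it.

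Third, a reader might split the sample by vendor as well as version and quote about ±10 points (246/4, about 61 DR-positives each). Two products are in use from the start whether or not the algorithm changes, so that figure is not a consequence of this point.

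Fourth, version logging and reporting by version are commonly left to an analysis plan. That is right, and their absence is not the fault. The fault is the stated intention to adjust the algorithm on accuracy data within its own validation.

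**Conclusion.** The point holds in a limited form. As written, the plan permits changes to the algorithm, guided by accuracy data, in the study that validates it, and it sizes one accuracy estimate as though the tool were fixed. If a change occurs during accrual, pooled sensitivity and specificity mix versions and may describe none. The ±5-point margin from 246 DR-positives then applies to no single version. It would be about ±7.1 points each for one update halfway, which is an assumption. The figures 246 and 1230 are themselves correct.

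Optimism is a possibility, conditional on images used for adjustment being counted in the adjusted version's accuracy. The assumed model puts it at roughly 0.9 to 2.3 points.

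The harm is limited to the AI accuracy outcomes. The comparison of disease staging rests on the first eye consultation and is largely unaffected.

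**What to change.** From now until the 1230-patient validation set is complete, hold each vendor's algorithm version and operating threshold fixed, and defer the adjustments described under Limitations of the study.

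For images already taken, or where an update cannot be avoided:

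- record the version and date of change, from vendor records where needed;
- use the AI output that was live at screening;
- report accuracy by version;
- evaluate an updated version only on images taken after the update.

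The cost is a protocol amendment, which the Ethics section makes subject to ethics committee clearance, a version field in the data portal, and work with the vendors to establish which versions scored past images. A lock cannot reach back over recruitment to date, so that part depends on those records. Algorithm improvements are delayed, and any per-version estimate is less precise than planned. Central grading of all images, with changed diagnoses passed to patients, continues meanwhile.

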## Conclusion

The study findings have the potential to impact national programs like Ayushman Bharat by demonstrating the feasibility of integrating AI-enabled diabetic retinopathy screening into routine care. Evidence on accuracy, cost-effectiveness, and optimized referral pathways could enhance resource utilization and accessibility. Additionally, the results may inform policy decisions on reimbursing AI-assisted screening by trained non-medical technicians, contributing to broader coverage and earlier detection of DR nationwide.
